### Statistical analysis plan (SAP)

*MRI data analysis*. The MRI protocol includes the accumulation of multiple images using various MRI modalities as described in Table 3. The modalities are: brain structural MRI (T1 and T2 weighted), cerebellum structural MRI (using the same brain images but cerebellum-specific processing pipelines), brain diffusion MRI, brain QSM, spinal cord structural MRI, spinal cord diffusion MRI and spinal cord MRS. For each of these modalities, all data from all seven sites will be processed by a single site to ensure consistent data processing.

Brain morphometry (structural imaging) will be performed using FreeSurfer [68, 69] to determine brain total volume, total white matter volume and total grey matter volume. Cerebellum morphometry, performed using ACAPULCO [70], to determine the total cerebellar volume while SUIT [71] will be used to calculate the volume of left and right cerebellar peduncles. Brain DTI data will be analysed using FMRIB Software Library (FSL) [69, 72] to determine the fractional anisotropy (FAn) and mean, axial and radial diffusivity (MD, AD, RD) of the left and right SCP. Brain QSM data will be reconstructed using the JHU/KKI QSM Toolbox v3.0 from the MATLAB suite [73, 74], and the left and right dentate nucleus will be segmented manually [13].

Spinal cord morphometry will be performed on spine T2 images using the Spinal Cord Toolbox (SCT) [75]. Spinal cord DTI data will be analysed using FSL and SCT. Spine MRS data will be analysed using the linear combination of model spectra (LCModel) [76, 77].

Each of these analysis methods will be considered independently. The *p* values will be corrected for type 1 error inflation using Stepdown Bonferroni testing within each modality.

Statistical analysis.

#### Analysis of cross-sectional differences at baseline

Individuals with FRDA and control groups will be compared at baseline using adjusted and unadjusted analyses. For unadjusted analyses, the two groups will be compared using the two-sample Student’s t-test or using the Mann-Whitney U-test for those variables that exhibit substantial skewness or otherwise do not match the assumptions of the two-sample t-test. For adjusted analysis a linear modelling approach will be used to predict case/control status, with demographic variables and site effects as covariates. This analysis will be conducted across all age groups represented in the study design, further enabling the possibility to observe differences in biomarkers between children and adults with FRDA and matched control participants. The baseline analysis provides the starting point from which functions such as rate of change can be derived for each of the parameters.

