### Study design

The TRACK-FA study will involve the participation of children and adults with genetically confirmed FRDA and control participants. Participants will be allocated to one of four groups based on their age: ≥ 18 years, 11–17 years, 8–10 years, and 5–7 years. Control participants will be matched at the cohort level to the FRDA participants for age, sex, handedness, and years of education. A recruitment ratio of 1:1 (FRDA: control) will be used for those aged 5–10 years and a 2:1 ratio (FRDA: control) will be used for participants ≥ 11 years of age.

We aim to recruit a total of 200 individuals with FRDA and 104 control participants across seven testing sites. This number was informed by a power analysis (see below) and necessitated a multi-site collaborative network to achieve this goal. All participants will then be assessed at three visits [Visit 1 (V1), Visit 2 (V2), Visit 3 (V3)] with identical assessments; each visit will take place approximately 12 months apart and no more than two months before or after the 12-month interval.

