#### Adjustment for potential site differences

Differences between sites will be examined at baseline, for each primary outcome using a mixed linear model with a random effect of site and fixed effects of age, sex, education, disease severity and other important covariates across individuals with FRDA and control participants and for control participants only. If site differences are detected, we will include site as a random effect within a mixed modelling approach for analyses involving that outcome. This is an important aspect in ensuring robustness in clinical trial ready neuroimaging biomarkers. Furthermore, for a biomarker to be clinical trial ready imaging measures must be reproducible, robust to scanner differences and sensitive to disease-related change. Adhering to these criteria allows the biomarkers to be used in multiple clinical trial contexts, e.g.: defining a clinical trial population Examining differences in data between sites will allow for this distinction to be made and internally validate the measures and identify biomarkers that are most sensitive to change over time in those in the earlier stages of FRDA.

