#### Assessing the association between variables at baseline

The associations between variables will be assessed at baseline. For outcomes that have nominally significant differences between FRDA and control groups at baseline, we will assess their relationship with the number of GAA repeats on both alleles, age of onset and disease duration using Pearson or Spearman’s rank correlation. For instance, this analysis can be used to determine whether a monotonic relationship exists between a biomarker and disease severity. We will further assess the correlations between imaging and blood biomarkers with cognitive assessments for participants using a linear modelling framework.

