#### Assessing the longitudinal changes over time

The within-person longitudinal slopes across the multiple visits will be estimated using a mixed linear model in which the slope for each participant is treated as a random effect. Within this framework we will assess the significance of a fixed effect that captures the difference in mean slope for individuals with FRDA with respect to controls. Due to the participant demographic in this study the analysis of within person slopes can give an indication of how age of onset and disease stage/severity can influence the subsequent clinical changes that occur within the parameters of participant demography.

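### The adjusted baseline model makes case/control status the response, so it gives no adjusted FRDA–control difference or confidence interval for any biomarker

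*Protocol article*

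**What the plan says.** The section *Analysis of cross-sectional differences at baseline* in the protocol article opens with its purpose: "Individuals with FRDA and control groups will be compared at baseline using adjusted and unadjusted analyses". For the unadjusted part, "the two groups will be compared using the two-sample Student’s t-test or using the Mann-Whitney U-test", so the biomarker is the measured outcome and group is the factor. For the adjusted part, "a linear modelling approach will be used to predict case/control status, with demographic variables and site effects as covariates". The section then expects the analysis to run across all age groups, "further enabling the possibility to observe differences in biomarkers between children and adults with FRDA and matched control participants", which is the subject of Objective 2.

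Three neighbouring sections bear on the point:

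- *Adjustment for potential site differences* describes a separate check of the scanning centres: "Differences between sites will be examined at baseline, for each primary outcome using a mixed linear model with a random effect of site". Site is carried forward as a random effect for any outcome in which site differences are detected.
- *Assessing the longitudinal changes over time*: "we will assess the significance of a fixed effect that captures the difference in mean slope for individuals with FRDA with respect to controls".
- *Assessing the association between variables at baseline*: the correlation analyses are run "For outcomes that have nominally significant differences between FRDA and control groups at baseline".

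**The concern.** The unadjusted and adjusted analyses are presented as two versions of one comparison, but they point in opposite directions. The t-test asks how far the biomarker differs between groups. The adjusted model asks how well group membership can be predicted. Group membership was set by recruitment, and under *Study design* "Control participants will be matched at the cohort level to the FRDA participants for age, sex, handedness, and years of education". As worded, the model regresses a recruited status on site and on demographic variables of the kind used for matching.

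At stake is the adjusted baseline effect size for every imaging measure, with its interval. A reader of a biomarker study needs that figure to judge how far FRDA and control values lie apart once age, sex, education and scanner site are allowed for. It is also what the child/adult comparison with matched controls calls for.

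**Working it through.** The plan states no figure on this point, so there is none to reproduce. The check is whether any reading of the sentence delivers an adjusted difference, and whether another section supplies one.

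**1. Literal reading.** Response: case/control status. Predictors: demographics and site. No biomarker appears, so no biomarker estimate, interval or test comes out.

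**2. Does another section supply the model?** The site model has each primary outcome as response, but it examines site differences and does not list group among its named fixed effects. The longitudinal model has group as a fixed effect in the usual direction, but for slopes. Neither is an adjusted baseline comparison of the groups.

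**3. Charitable reading: the biomarker is added as a predictor.** Inputs from *Study design*: 200 FRDA, 104 control, seven sites. Assumed: residual SD 1; age, sex and fixed site covariates; true adjusted differences of 0.3, 0.8 and 1.5 SD; 1000 simulated datasets for each. Mean results:

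| True difference (SD) | Biomarker as response: group coefficient | Status as response, OLS: biomarker coefficient | Status as response, logistic: log-odds per unit | OLS t, either direction |
|---|---|---|---|---|
| 0.3 | 0.298 | 0.066 | 0.312 | 2.43 |
| 0.8 | 0.802 | 0.158 | 0.842 | 6.55 |
| 1.5 | 1.501 | 0.224 | 1.587 | 12.23 |

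Only the first model returns the adjusted difference. In the reversed OLS model, 0.2%, 3.5% and 12.4% of fitted values fell outside 0 to 1.

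**4. Closed-form check of the OLS column (no covariates).** With within-group SD 1, difference D and FRDA share p, the coefficient is p(1−p)D / (1 + p(1−p)D²). Here p = 200/304 = 0.658, so p(1−p) = 0.2251.

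- D = 0.3: 0.0675 / 1.0203 = 0.066
- D = 0.8: 0.1801 / 1.1440 = 0.157
- D = 1.5: 0.3376 / 1.5064 = 0.224

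The coefficient is not proportional to D: a fivefold rise in the true difference (0.3 to 1.5) raises it 0.224/0.066 = 3.4 times. Under OLS it also depends on the recruitment ratio. At D = 1 it is 0.2251/1.2251 = 0.184 with 200:104, and 0.25/1.25 = 0.200 with 1:1.

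**5. What happens to the test.** In either OLS direction, t = r√(df/(1−r²)), where r is the partial correlation of biomarker and group given the same covariates. Since r is symmetric, t and the p-value are identical; the largest gap in the simulations was about 1.6 × 10⁻¹³. This holds for OLS with site as fixed covariates. It is not claimed for a random site effect or for logistic regression.

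**The case against.** The strongest reply is that this is a slip of wording in a condensed article. The heading, the opening sentence and the reference to biomarker differences all show that an ordinary adjusted comparison was meant. The neighbouring site and longitudinal models have the imaging measure as response, and a full analysis plan may hold the right equation. That makes the intention plausible. It does not remove the error, because the article states which variable is predicted and states the wrong one. This is not a detail left out for a fuller document.

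A second reply is that a linear modelling approach may loosely mean logistic regression, the usual model for case/control status. Under that reading, a misspecified 0/1 response is no longer an issue, and the slope does not depend on the case:control ratio; both of those criticisms hold only under OLS. The slope is still in log-odds per biomarker unit. It looks close to the true difference in the table because the residual SD was set to 1.

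A third reply is that little follows downstream. This largely stands. The stated decision use of the baseline comparison is selecting outcomes by nominal significance for the correlation analyses. With the biomarker as a predictor, OLS and fixed site covariates, that selection would be the same in either direction.

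A reader might also infer that biomarkers would be ranked wrongly. The documents do not support this. No section ranks biomarkers by a baseline coefficient, and Objective 1 concerns sensitivity to change over time. The OLS coefficient turns down only beyond a difference of about 2.1 SD; the article gives no baseline effect of that size, and over 0.3 to 1.5 SD the coefficient rises steadily.

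**Conclusion.** The point holds in a limited form. As written, the adjusted baseline analysis has response and factor reversed and names no biomarker. Taken literally, or with the biomarker added as a predictor under OLS or logistic regression, it reports no adjusted FRDA–control difference and no interval for any biomarker, and no other section provides them.

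A reader might infer that adjusted baseline inference is lost altogether. That goes too far: if the biomarker is entered as a predictor under OLS with fixed site covariates, the adjusted p-value is unchanged. What is lost is the estimate and its interval. The slope analysis and the 12-month difference-in-difference analysis are unaffected. The simulated sizes rest on the assumed SD, covariate structure and effect sizes. The conclusion about model direction does not.

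**What to change.** Replace the sentence on the adjusted analysis with wording such as:

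> For the adjusted analysis, each baseline biomarker will be the response in a linear model with group (FRDA or control) as the factor of interest and age, sex, education and site as covariates. Where site differences are detected for an outcome, site will enter as a random effect, as set out under *Adjustment for potential site differences*. The adjusted mean difference and its 95% CI will be reported.

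The authors should also say whether handedness, which is a matching variable, belongs among the covariates.

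A group-by-age-group term could be added for the child/adult question, but it is optional. It would be imprecise for ages 5–10, where *Status and timeline of the study* plans only eight FRDA participants.

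The cost is one sentence. No extra data, visits or participants are needed.

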#### Adjustment for potential site differences

Differences between sites will be examined at baseline, for each primary outcome using a mixed linear model with a random effect of site and fixed effects of age, sex, education, disease severity and other important covariates across individuals with FRDA and control participants and for control participants only. If site differences are detected, we will include site as a random effect within a mixed modelling approach for analyses involving that outcome. This is an important aspect in ensuring robustness in clinical trial ready neuroimaging biomarkers. Furthermore, for a biomarker to be clinical trial ready imaging measures must be reproducible, robust to scanner differences and sensitive to disease-related change. Adhering to these criteria allows the biomarkers to be used in multiple clinical trial contexts, e.g.: defining a clinical trial population Examining differences in data between sites will allow for this distinction to be made and internally validate the measures and identify biomarkers that are most sensitive to change over time in those in the earlier stages of FRDA.

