Depending on age, one of two MRI protocols will be used: the first protocol, approximately 90 minutes long, will be used in all participants aged >10 years. The second, approximately 30 minutes long and designed to be less taxing for younger children, will be used in the 5–10 years age group. The young child protocol only includes anatomical scans (brain and spinal cord), but no diffusion MRI, brain QSM, or spinal cord MRS. Brain T1, T2 and diffusion acquisitions are based on those used in the Human Connectome Project [36]. Brain QSM acquisition was optimised to provide excellent image quality and contrast with 0.9 isotropic resolution. The spinal cord T2, diffusion and MEDIC acquisitions are based on a recently published spinal cord protocol [37]. The spinal cord MRS is based on a semi-LASER sequence developed at the University of Minnesota [54], with addition of metabolic cycling. The specific MR sequences, acquisition time, and key parameters for each sequence are outlined below in Table 3. These sequences will be used to acquire the outcome measures provided in Table 4.

**Table 3 pone.0269649.t003:** TRACK-FA protocol used to obtain cervical spinal cord and brain MRI data.

Data	Sequence	Resolution	Main parameters	Acq. time
Spine T2	3D SPACE	0.8 mm iso	TE 120 ms, TR 1500ms, iPAT 3	4’02”
Spine MRS battery (includes power calibration and shimming)	semiLASER (CMRR)	8 x 6 x 33 mm	TE 30 ms, TR 2500 ms, NA 160	8’10””
Spine diffusion	2D SE-EPI with ZOOMit	0.9 x 0.9 x 5mm	TE 61 ms (Skyra 92ms), TR 620 ms (Skyra 680 ms), 5 concatenations, 30 dirs, b = 800, 5 b0 On Skyra, NT = 2 for diffusion weighted volumes (b = 800)	4‘(AP) + 1’ (PA) (b0 only) (with pulse trigger) On Skyra these times are nearly doubled)
Spine MEDIC	2D multi-echo	0.5 x 0.5 x 5mm	TE 14 ms, TR 600 ms, NA 2, 3 echoes, iPAT 2	4’45”
Brain T1	3D MPRAGE	0.8 mm iso	TE 2.2ms, TR 2400 ms, TI 1000 ms, iPAT 2	6’38”
Brain T2	3D SPACE	0.8 mm iso	TE 563ms, TR 3200 ms, iPAT 2	5’57”
Brain diffusion	Multiband EPI (CMRR)	1.5 mm iso (Skyra 1.7 mm iso)	TE 89ms (Skyra 102 ms), TR 3230 ms (Skyra 3366 ms), MB 4, 197 dirs, 2 shells, b = 1500/3000, 6 b0	5’37” (AP) + 5’37” (PA)
				Skyra 5’52” (AP) + 5’52” (PA)
Brain QSM	3D GRE	0.9 mm iso	TE1/TE2/TE3/TE4 = 3.7/9.7/15.8/21.9 ms, TR 27ms, iPAT 2	7’22”

* For participants 10 years old and younger, only anatomical data (highlighted in grey) are collected.

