** The times above are data acquisition times for each sequence and do not include time for adjustments (e.g., scout images, shimming, power calibration) and ROI planning.

**Table 4 pone.0269649.t004:** The brain regions, modalities, and outcome measures for the TRACK-FA MRI protocol.

Region	Modality	Outcome measure
Brain	Structural MRI (Brain morphometry)	Total brain volume
		Total white matter volume
		Total grey matter volume
Brain	Structural MRI (Cerebellum morphometry)	Total cerebellar volume
		Superior cerebellar peduncles volume
Brain	Quantitative susceptibility mapping (cerebellum only)	Iron concentration in the dentate nuclei*
		Volume of the dentate nuclei*
Brain	Diffusion MRI	Superior cerebellar peduncle fractional anisotropy*
		Superior cerebellar peduncle mean diffusivity*
		Superior cerebellar peduncle radial diffusivity*
		Superior cerebellar peduncle axial diffusivity*
Spinal cord	Structural MRI (morphometry) (Values extracted from the spine T2 image)	Cross sectional area of the cervical spinal cord, averaged over two C2-C3
Spinal cord	Diffusion MRI	Total White matter changes in fractional anisotropy*, mean diffusivity*, radial diffusivity*, axial diffusivity*
Spinal cord	Magnetic resonance spectroscopy (Voxel positioned over C4-C5)	Total N-acetyl-aspartate (tNAA)/myo-inositol (mIns) ratio*

(*) only undertaken for participants > 10 years of age.

*Clinical measures to assess secondary outcomes*. Individuals with FRDA will undergo assessments using neurologic scales and functional measures outlined in Table 5. Additionally, all participants enrolled will undergo speech assessments. The speech assessment is conducted using the REDENLAB software [58], consisting of an adult battery (for those aged ≥ 18 years) and a paediatric battery (aged 5–17 years).

**Table 5 pone.0269649.t005:** Neurologic and functional measures completed by TRACK-FA participants.

Assessment	Description
FARS Staging for Ataxia Scale	This assessment indicates the impact of FRDA on function.
mFARS neurological exam (FARS subscale)	The mFARS comprises four subscales (bulbar, upper limb coordination, lower limb coordination, and upright stability) and has a maximum score of 93 [34]
FARS Activities of Daily Living (ADL)	The ADL, assessed in a structured guided interview setting, is a component of the FARS and aims to quantify essential and routine aspects of self-care, The ADL comprises 9 questions and has a maximum score of 36 [51]

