Scale for Assessment and Rating of Ataxia (SARA)	The SARA is a semi-quantitative assessment of ataxia, measuring ataxia of upper limb, lower limb, gait, balance and speech. It has eight items, with the total score ranging from zero (no ataxia) to 40 (severe ataxia) [55]
9- Hole-Peg test (9HPT)	This test examines finger dexterity and involves placing and removing nine pegs in a pegboard in the quickest possible time. The 9HPT has high intra- and inter-rater reliability and is the most commonly used measure of upper limb function in FRDA [56]
Low-Contrast Sloan Letter Chart (LCSLC) testing	Contrast letter acuity testing for vision will be performed using the low-contrast Sloan letter charts (LCSLC–Precision Vision, La Salle, IL) [57]. Binocular LCSLC measurements will be obtained at 2 meters for each of three contrast levels (100%—equivalent to high-contrast visual acuity, 2.5%, and 1.25% contrast levels)
*Measures of Dysarthria	Dysarthria is measured using speech testing. The specific speech testing software used is the REDENLAB software [58] consisting of an adult and paediatric battery

*Clinical assessments undertaken by both individuals with FRDA and control participants.

*Cognitive and mood assessments to assess secondary outcomes*. Individuals with FRDA and control participants will undergo a range of cognitive and mood assessments for the TRACK-FA study. These assessments have been outlined in Table 6. Paediatric participants aged < 8 years will not be required to undergo measures of cognition or mood.

**Table 6 pone.0269649.t006:** The cognitive and mood assessments completed by TRACK-FA participants.

Assessment	Description
Cerebellar Cognitive Affective/Schmahmann Syndrome Scale (CCAS)	The CCAS is a 10-item scale assessing the executive, visual spatial and linguistic components of cognitive control and affect [59]. This assessment will be only completed by those in the ≥18 age group
Hayling Sentence Completion Test (HSCT)/ Junior HSCT	The HSCT will be completed by those in the ≥ 18 age group, while the Junior HSCT [60] will be administered to the 11–17 and 8–10 age groups. The HSCT is a measure of response initiation and suppression [60–62], and has demonstrated sensitivity to detect cognitive deficits in FRDA [63]

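### Site should enter every FRDA-control imaging model as a design factor. The plan makes it conditional on a baseline site test that cannot see differences in change and cannot be fitted as worded in controls

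*Protocol article*

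**What the plan says.** Under Adjustment for potential site differences, the Protocol article sets out a check and then a rule. The check: "Differences between sites will be examined at baseline, for each primary outcome using a mixed linear model with a random effect of site". Its covariates and populations are "fixed effects of age, sex, education, disease severity and other important covariates across individuals with FRDA and control participants and for control participants only". The rule: "If site differences are detected, we will include site as a random effect within a mixed modelling approach for analyses involving that outcome". No criterion for detection is given.

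Other sections bear on this:

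- **Analysis of cross-sectional differences at baseline.** The adjusted comparison is made "with demographic variables and site effects as covariates", with no condition attached.
- **Assessing the longitudinal changes over time.** The slope model has a random slope per participant and a fixed effect for the FRDA-control difference in mean slope. No site term is named.
- **Difference-in-difference analyses.** The 12-month changes are compared by a two-sample t-test or Mann-Whitney test. Neither can carry a site term.
- **MRI scanning and Table 3.** Scanners are Siemens Skyra, Siemens Prisma or Philips Ingenia. Some acquisition settings differ by design. Brain diffusion resolution, for example, is "1.5 mm iso (Skyra 1.7 mm iso"), and its echo time is 89 ms, or 102 ms on Skyra.
- **Clinical measures and Table 5.** "Individuals with FRDA will undergo assessments using neurologic scales and functional measures outlined in Table 5". One item, dysarthria, is marked with the footnote "Clinical assessments undertaken by both individuals with FRDA and control participants".

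**The concern.** There are three difficulties, and none depends on an assumed figure.

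1. **Site is treated as a hypothesis, although it is part of the design.** The protocol itself fixes scanner and sequence differences. Deciding outcome by outcome whether to adjust for them, from the same data, leaves the final model undefined in advance. It also conflicts with the unconditional site adjustment planned for the baseline comparison.
2. **The check looks at level, while Objective 1 is about change.** Two sites can agree at baseline and still diverge over 24 months, and the check would not register it.
3. **The check cannot be fitted as worded.** Disease severity is listed as a covariate in a model for controls only, yet the severity scales are given to participants with FRDA.

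At stake is whether the FRDA-control contrasts are protected against scanner effects. Controls are matched at cohort level (Study design), so a similar FRDA-to-control ratio at each site is not assured.

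**Working it through.** **Inputs from the document.** 200 participants with FRDA and 104 controls, 304 in all; seven sites; 20% attrition. If balanced, that is 304/7 = 43.4 participants and 104/7 = 14.9 controls per site. The document gives no power figure for the site check, so there is none to reproduce.

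**Assumptions.** Alpha 0.05 for detection; ICC (share of variance lying between sites) from 0.02 to 0.20; four covariate degrees of freedom. The document states none of these.

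**Power of the check.** For a random-site one-way model with k = 7 sites and n per site, F is distributed as (1 + n × ICC/(1 − ICC)) × F(6, N − 7 − 4). Power is therefore P[F(6, N − 11) > Fcrit/(1 + n × ICC/(1 − ICC))].

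- Controls, ICC 0.05: Fcrit(6, 93) = 2.198; multiplier 1 + 14.86 × 0.0526 = 1.782; P(F > 1.233) = 0.30.
- Controls, ICC 0.10: multiplier 1 + 14.86 × 0.1111 = 2.651; P(F > 0.829) = 0.55.
- Pooled, ICC 0.05: Fcrit(6, 293) = 2.130; multiplier 1 + 43.43 × 0.0526 = 3.286; P(F > 0.648) = 0.69.
- Pooled, ICC 0.10: multiplier 1 + 43.43 × 0.1111 = 5.825; P(F > 0.366) = 0.90.

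| ICC | 0.02 | 0.05 | 0.10 | 0.20 |
|---|---|---|---|---|
| Controls only (104) | 0.13 | 0.30 | 0.55 | 0.83 |
| Pooled (304) | 0.35 | 0.69 | 0.90 | 0.98 |

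With unequal sites (30, 20, 15, 12, 10, 8 and 5% of participants), simulation gives 0.13, 0.28, 0.52 and 0.80 for controls and 0.33, 0.65, 0.88 and 0.97 pooled.

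**Level against change.** Simulated with 160 FRDA and 83 control completers (80% of 200 and of 104). When sites differed in change but not in level, the baseline test flagged a site difference in about 5% of runs, which is its false-positive rate. It carries no information on that question.

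**Effect on type I error.**

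- *Baseline level.* Null simulations used 3,000 runs per setting, ICC 0.05 and 0.10, and mild to strong imbalance in case mix between sites. Site was kept if either planned test (pooled or controls only) was significant. The two-step rule then rejected in about 4 to 6% of runs overall. Both tests were negative in about 30% of runs at ICC 0.05 and 10% at ICC 0.10. Within those runs the error reached about 8 to 9%, and only under strong imbalance. At ICC 0.10 that conditional figure rests on only some 300 runs (3,000 × 0.10), so it is rough. Including site always gave about 4 to 5% in every setting.
- *Change.* Leaving site out gave 0.048 to 0.062 against a nominal 0.05, with equal or mildly unequal case mix across sites.

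**The severity term.**

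- In the controls-only model, severity is either missing or the same for everyone. Its coefficient cannot be estimated.
- In the pooled model, severity is missing for controls, and a complete-case fit then loses them. If instead it is coded zero, it largely overlaps with diagnosis. Diagnosis is not among the named terms: "fixed effects of age, sex, education, disease severity and other important covariates across individuals with FRDA and control participants".

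**The case against.** The case for leaving the text alone has substance.

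- **The harm is small.** With both planned tests used, overall type I error stays near nominal. This stands, and it limits the weight of the point.
- **Power is not uniformly low.** The pooled test has 90% power at ICC 0.10. This stands: weak detection is a feature of the controls-only test and of small site variance.
- **Fixed Skyra settings are constant over time.** If their effect is purely additive, it cancels in within-person change, and it is the kind of difference a baseline test looks for. This stands for additive effects. It does not cover site differences in rate of change, and it gives no reason to test for a difference already written into the protocol.
- **There are safeguards.** Sequences are harmonised and piloted, each modality is processed at a single site, and phantoms are scanned monthly with correction at the affected site. These reduce site effects but do not settle which model is used.
- **Severity coding is a detail for the analysis plan.** Stage 0 in Table 2 means normal and could serve for controls, and the open-ended covariate list could include diagnosis. This partly stands: a reader might infer that all 104 controls would be lost from the pooled fit, but that depends on coding. The controls-only model is not rescued, because a constant cannot be estimated either.

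A reader might also infer a serious inflation of type I error, of the order of 5 to 16%. Figures of that size arise from an unadjusted baseline t-test after a negative controls-only test. The documents do not support that reading. The site check also has a pooled arm, the unadjusted baseline comparison is unadjusted by intention, and the adjusted one always carries site.

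**Conclusion.** The point holds as a correctable weakness in model specification. It does not show that the FRDA-control comparisons are invalid. The conditional rule conflicts with the unconditional site adjustment at baseline, and it rests on a test that cannot detect site differences in change. The test's covariate list is also unusable in controls. These conclusions follow from the text alone.

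The size does depend on assumptions. At alpha 0.05 and ICC 0.05 to 0.10, a true site difference is missed in about 45 to 70% of cases in controls only and 10 to 31% in the pooled sample. The consequence for type I error is small unless the FRDA-to-control mix differs strongly between sites, and the documents neither show nor exclude such imbalance.

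**What to change.** 1. Include site in every FRDA-control model for every imaging outcome, whatever the site test shows. This covers the longitudinal slope model and a regression version of the 12-month change comparison. Fixed or random is a matter of preference.
2. Bring the two baseline sections into line, so that site is unconditional in both.
3. Keep the baseline site test as a descriptive report. Give site-by-time as a sensitivity analysis.
4. Drop disease severity from the controls-only site model. In the pooled model, use diagnosis plus severity nested within FRDA (centred in FRDA, zero for controls).

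The cost is a change of wording and about 6 degrees of freedom (7 sites − 1) if site is fixed, from roughly 240 to 300 participants. The site-by-time sensitivity analysis uses about 6 more.
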